### Qualitative Data Analysis

Qualitative data will be analyzed using thematic analysis following the guidance of Miles and Huberman and will be conducted using NVivo qualitative analysis software [33]. All interviews will be audio-recorded and transcribed verbatim. A researcher will remove all identifying information from the transcripts, including any references to patients, clinicians, or local services.

An inductive approach will be used to provide new insights and a richer understanding of the data without using preconceived categories. Two members of the research team will first familiarize themselves with the transcripts. Open coding will be used (making notes and headings in the text to describe the content). Similar codes will be grouped under themes, and the identified themes and subthemes will then be checked and refined. Interrater reliability in applying second-level codes (or categories) will be calculated for 20% of the data.

### Reporting of Adverse Events

For this RCT, we will adopt the World Health Organization’s definition for an adverse event: “Any untoward medical occurrence in a patient or clinical investigation subject administered a pharmaceutical product and which does not necessarily have to have a causal relationship with this treatment” [34]. Adverse events and the need for urgent safety measures are not anticipated.

#### Adverse Events

Any adverse events will be recorded in the main research file and in the participant’s clinical records, if appropriate, and the participant will be followed up by the research team. We will establish an adverse event registration form based on REDCap in which research assistants can make a report of any adverse event for the RCT.

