#### Recruitment and Informed Consent

Each study site will include a coordinator who will recruit the clinicians for the study. A research assistant will recruit the adolescents, guide all participants through the informed consent process, and assess the outcomes at 3 defined time points (baseline, 6 months, and 9 months post randomization). A wider administrative staff member will schedule the follow-ups and provide the clinicians’ caseload to the research assistant to identify potential adolescent participants.

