### Intervention

The enrolled clinicians will be contacted and invited to a web-based meeting on a free videoconferencing platform such as Zoom or Microsoft Teams with a researcher who will re-explain the objectives of the RCT and answer any questions or concerns that are raised.

Clinicians randomized to the intervention arm will use DIALOG-A with the adolescents once per month for 6 months. Clinicians allocated in this arm will receive a tablet, with the DIALOG-A app already preloaded. Each DIALOG-A session will last approximately 20 minutes and will take place face to face with the clinician. Where it is not possible for a face-to-face consultation to occur, a web-based consultation will be conducted in line with standard care procedures within the health care service. In each session, the clinician will ask the patient to rate all the domains on the DIALOG scale, which will then be followed by the 4-step solution-focused approach. After completing the 6-month intervention with the DIALOG-A app, clinicians and adolescents can continue using the intervention depending on their needs, and this will be documented and considered in the analysis.

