### Randomization

To reduce the potential for contamination, the unit for randomization will be the clinician. Clinicians will be randomized 2:1 to either the intervention (12 clinicians:72 adolescents; to have DIALOG-A sessions once per month for 6 months) or to the treatment-as-usual control group (6 clinicians:36 adolescents; appointments scheduled as and when needed, without DIALOG-A or specific assessments). For existing patients, who are already on the caseload, adolescent participants will be recruited and baseline assessments conducted prior to their clinician being randomized. Individuals who are new to the service and are not on the existing caseload of a clinician will be randomly assigned to either the intervention or control arm and then to an appropriate clinician, following completion of the baseline measures. We will record the number of adolescent participants who are recruited and individually randomized.

Clinicians and adolescents will not be blinded to allocation due to the nature of the intervention. However, to reduce bias, randomization will be carried out by a blinded independent statistician at the Unit for Social and Community Psychiatry, Wolfson Institute of Population Health, Queen Mary University of London. Baseline data collection will occur before randomization, and all research assistants involved in outcome data collection will be blinded to allocation. We will additionally record the number of postrandomization recruits; for example, individuals who were recruited after their clinician has been randomized.

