#### Quarterly Safety Reporting

The local PI will send over quarterly reports as required by the REC, using their existing templates and guidelines. These will be additionally monitored by the international trial steering committee, who will assume the role of a data monitoring and ethics committee.

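### The adverse event form goes to blinded outcome assessors who have no planned contact with adolescents during the 6-month treatment period, so events may surface late or through unblinding reports

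*Protocol article*

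**What the plan says.** Under Adverse Events, the article sets up a REDCap form on which "research assistants can make a report of any adverse event for the RCT". The sentence before it provides that "Any adverse events will be recorded in the main research file and in the participant’s clinical records, if appropriate", with follow-up by the research team. The research assistant is the only role named in connection with the form.

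Under Recruitment and Informed Consent, the research assistant recruits adolescents, takes participants through consent, and is to "assess the outcomes at 3 defined time points (baseline, 6 months, and 9 months post randomization". No scheduled contact between these assessments is described.

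Under Randomization, "all research assistants involved in outcome data collection will be blinded to allocation", whereas "Clinicians and adolescents will not be blinded to allocation due to the nature of the intervention".

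Under Intervention, "Clinicians randomized to the intervention arm will use DIALOG-A with the adolescents once per month for 6 months". The article describes control contact in two ways. Randomization says "appointments scheduled as and when needed, without DIALOG-A or specific assessments". Treatment-as-Usual Control says that frequency varies but averages about one consultation a month.

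Under Quantitative Data, clinicians complete a Clinical Global Impression rating each time they see a patient, with no restriction by arm and no stated adverse event item. Under Quarterly Safety Reporting, "The local PI will send over quarterly reports as required by the REC", and the steering committee, acting as data monitoring and ethics committee, also monitors these. The Results section lists adverse events among the things to be reported.

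**The concern.** Three role assignments pull against each other. The person who files the adverse event form is also the blinded assessor of the primary outcomes, and has no planned contact with the adolescent while treatment is being given. The people who do see the adolescent in those months are unblinded clinicians, for whom the article states no part in adverse event reporting.

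Two things are at stake. The first is timeliness: the quarterly reports and the steering committee's safety role have no planned feed of events during treatment, in a population where the article itself foresees severe depression and suicide risk. The second is blinding: a clinician or adolescent who describes an event that arose in or around a DIALOG-A session tells the assessor the arm.

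A third, weaker issue is comparability. If events come to light mainly through clinical contact, and contact or its structure differs by arm, recorded counts may partly reflect the opportunity to report.

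**Working it through.** The article gives no figure for adverse event ascertainment, so there is none to reproduce. The check uses the visit schedule and a side-by-side reading of the sections.

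**Inputs from the article:** research assistant assessments at months 0, 6 and 9; treatment in months 0 to 6; safety reports every 3 months; six monthly sessions in the intervention arm; control contact averaging about monthly in one section and on demand in another.

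**Assumptions:** event times are uniform between assessments, and the report calendar is unrelated to the date an adolescent enters.

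**Delay if an event surfaces only at a scheduled assessment**
- Event at month t of treatment: wait w = 6 − t. The maximum is 6 − 0 = 6 months and the mean is 6/2 = 3.0 months.
- Share waiting more than 1 month: 5/6 = 83%. Share waiting more than 3 months: 3/6 = 50%.
- Between months 6 and 9: maximum 3 months, mean 3/2 = 1.5 months.

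**Quarterly reports passed during the wait**
- If w is 3 months or more (event in the first 3 months), at least one report date is certain to pass.
- If w is less than 3 months, a report date passes with probability w/3, which averages 0.5.
- Over the whole treatment period: 0.5 × 1 + 0.5 × 0.5 = 0.75. About three quarters of such events would miss at least one report.
- Example: an event at month 1 waits 6 − 1 = 5 months. It misses one report for certain and two with probability (5 − 3)/3 = 2/3.

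**Routes faster than the scheduled assessments**
- Participants hold the researcher's contact details throughout the study. This route is open to both arms, but it is passive and the adolescents know their allocation.
- Clinicians could tell the research team. They too are unblinded, and the article describes no path that bypasses the assessor.

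**Contact by arm**
- If control contact averages once a month, contacts over 6 months are 6 against 6, a ratio of 6/6 = 1.0.
- If control contact is on demand, the article gives no number, so no ratio can be derived.
- Apart from frequency, intervention sessions are structured, and Training and Supervision gives intervention clinicians at least 2 refresher sessions with the research side. No counterpart is described for control clinicians.

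**The case against.** The strongest reply is that this is a condensed article. Who prompts for events, how they reach the form and who may open it are details a full protocol may hold. The wording about research assistants is also permissive: it says who may file a report, not who alone may notice an event. Other provisions exist. Events may go into clinical records, participants can contact the researcher at any time, physicians review and monitor enrolled adolescents identified with severe symptoms or suicide risk, and the local principal investigator is responsible for safety reporting. The assessor-unblinding chain is conjecture, and adolescents who answer the questionnaires already know their arm.

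Much of this stands, and it limits the point. A reader might infer that the quarterly reports must be empty during treatment. The documents do not support that, because nothing confines those reports to events found at assessment visits. A reader might also infer that events will be counted more fully in the intervention arm. That is not shown either: the article's one statement of control frequency puts it level with the intervention sessions, the clinician rating applies to both arms, and any inflated rate ratio would need control visit counts and detection rates that the article does not give. The article also plans no between-arm test of adverse events.

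The reply does not dispose of the conflict between roles that are stated. The article assigns the form to research assistants, blinds them, and schedules them outside the treatment window. A longer document could add procedures, but this assignment would still need changing. The alternative routes are unsolicited or cover only adolescents already identified as at high risk, and the reports from clinicians and adolescents come from people who know the allocation.

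**Conclusion.** The point holds as a conflict of roles and a gap in planned collection. As written, adverse events during the 6 months of treatment either wait for the 6-month assessment or depend on passive reports from unblinded people to a blinded assessor. The wait is up to 6 months, with a mean of 3 months under uniform event times. Events in the first 3 months of treatment that wait for that assessment are certain to miss at least one quarterly report. These figures describe events that surface only at scheduled assessments; the share of events that would do so is unknown.

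The threat to assessor blinding is real but cannot be sized. Differential ascertainment is a risk, not a demonstrated bias. It rests on the structured contact in one arm and on the unresolved description of control contact, and its frequency component disappears if control contact is monthly. The plan should be changed on this point, but the point does not undermine the trial's validity as a whole.

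**What to change.** 1. Add a yes/no adverse event item to the Clinical Global Impression form that clinicians in both arms complete after appointments. Route a positive answer to the site coordinator or local principal investigator, in a REDCap form that outcome assessors cannot open. Use this stream for the quarterly reports.
2. At 6 and 9 months, put the same fixed adverse event questions to every adolescent in both arms, after the outcome scales are finished. Because an answer given at 6 months could unblind the same assessor for 9 months, either instruct adolescents not to mention the treatment they received or use a self-completed form that the assessor does not see. Base any between-arm description of adverse events on these answers, since the enquiry is identical in both arms.
3. Reconcile the Randomization and Treatment-as-Usual Control sections on how often control adolescents are seen.

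The cost is one item on an existing form, a short question set at two existing visits and a change to access rights. The downsides are a few minutes per visit and a higher reported event count, which should be expected when events are asked about systematically. No new staff or visits are needed.

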#### Serious Adverse Events

Serious adverse events are those that are “unexpected” and will be reported in accordance with the regulations of the research ethics committee (REC) and other relevant regulations in Colombia.

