### Participants

#### Inclusion Criteria

The inclusion criteria for clinicians will be as follows: (1) being aged 18 years or older, (2) having a medical qualification as a general practitioner or pediatrician, (3) having regular contact with adolescent patients with anxiety and depression, (4) having at least 3 months of experience in working with adolescents, and (5) having no plans to leave their current position within the next 6 months.

The inclusion criteria for adolescents will be as follows: (1) being aged 13 to 16 years; (2) currently experiencing anxiety and depression, which is defined as a cutoff score of ≥7 on the Self-Reporting Questionnaire [23]; and (3) having the capacity to provide informed assent.

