### Treatment-as-Usual Control

The intervention group will be compared to treatment-as-usual control. Clinicians in the control arm will follow the routine care provided for adolescents accessing primary care services. The frequency of the consultations during the duration of the RCT will vary depending on the clinical criteria of the respective clinician and the adolescent; however, this will be, on average, once per month.

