### Safety and Suicide Risk Reduction

Participants who decline to participate but may have severe depression, severe anxiety, or are at a risk of suicide will be treated in accordance with each clinical site’s procedures. For participants enrolled in the study who have been identified as having severe depression, severe anxiety, or being at a risk of suicide, the primary care physician will review and monitor the results of the screening. The participant will be managed in accordance with the primary care site’s usual protocols and guidelines.

Additionally, if the participant meets the criteria for severe depression or anxiety, or is identified as being at risk of suicide, treatment may be either administered by or coordinated with a psychiatrist (in accordance with the Colombian clinical guidelines of best practices). According to the primary care physician, an optional case review could be performed by the academic psychiatrists involved in this study. Figure 1 summarizes the participant flow chart during the RCT.

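### Serious adverse events are defined by being unexpected, and adverse events by drug exposure, so the protocol's wording cannot classify harms in this non-drug trial

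*Protocol article*

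**What the plan says.** Under Serious Adverse Events, the protocol article states: "Serious adverse events are those that are “unexpected” and will be reported in accordance with the regulations", meaning those of the research ethics committee and other Colombian rules. None of the safety sections, from Reporting of Adverse Events to Safety and Suicide Risk Reduction, gives a criterion based on the outcome of the event.

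Under Reporting of Adverse Events, the trial adopts a World Health Organization definition: "Any untoward medical occurrence in a patient or clinical investigation subject administered a pharmaceutical product". The same section adds: "Adverse events and the need for urgent safety measures are not anticipated".

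The treatments compared are not drugs. Under Intervention: "Clinicians randomized to the intervention arm will use DIALOG-A with the adolescents once per month for 6 months". Under Treatment-as-Usual Control: "The intervention group will be compared to treatment-as-usual control". Participants are aged 13 to 16 and, under Inclusion Criteria, are "currently experiencing anxiety and depression, which is defined as a cutoff score of ≥7 on the Self-Reporting Questionnaire". Safety and Suicide Risk Reduction provides for enrolled participants "identified as having severe depression, severe anxiety, or being at a risk of suicide".

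**The concern.** Seriousness and expectedness are separate attributes of an event. Using the second as the definition of the first gives wrong answers in both directions: a grave event that was foreseen is not serious, and a minor event that was not foreseen is.

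This matters here because the gravest harm in the population, suicidal behaviour, is also one that the protocol plans for. The steering committee acts as the data monitoring and ethics committee and needs a serious category that it can use. Proposed Sample Size says that the trial's main purpose is to gather what a full trial protocol needs, so a faulty definition could be carried forward.

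The drug-exposure wording adds a second problem. It makes the entry condition for an adverse event something that the trial does not administer.

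**Working it through.** No arithmetic applies, since the protocol states no figure tied to these definitions. The check sets the passages side by side.

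**1. What decides that an event is serious?** The Serious Adverse Events section gives one test, expectedness. Cross it with the consequence of the event:

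| Event | Serious by outcome | Reading A: unexpected means not foreseeable in this population | Reading B: none is anticipated, so all are unexpected |
|---|---|---|---|
| Grave, foreseeable | yes | no | yes |
| Grave, not foreseeable | yes | yes | yes |
| Minor, foreseeable | no | no | yes |
| Minor, not foreseeable | no | yes | yes |

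Reading A agrees with the outcome column in 2 of 4 rows. It fails on the grave, foreseeable event and on the minor surprise. Reading B also agrees in 2 of 4 rows: it loses no grave event, but it calls every event serious and so separates nothing. The rows are logical cases, not frequencies.

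**2. Can a suicide attempt fall in the first row?** Safety and Suicide Risk Reduction foresees suicide risk among enrolled adolescents. A person applying the rule could therefore judge an attempt to be expected, and under Reading A it would not be serious. The article does not say which reading applies.

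**3. Who can have an adverse event?** The adopted definition refers to a subject given a pharmaceutical product. DIALOG-A is an app-supported consultation and the control is routine care. Neither arm receives a study drug, so the definition does not describe the exposure under test.

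**4. Does another section repair this?**
- Adverse Events provides for recording any adverse event, with a REDCap form, but supplies no new definition of the term.
- Quarterly Safety Reporting sends reports to the ethics committee on that committee's templates, and the steering committee also monitors them. It gives no definition of seriousness.
- Overview of the Safety Reporting Responsibilities defers to ethics committee requirements, which are not shown.

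These sections add routes by which an event may be recorded and seen. None replaces the test of seriousness.

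**The case against.** The strongest reply is that the protocol anticipates no adverse events, so each one is unexpected, and a suicide attempt would be reported as serious. On that view the rule includes too much and loses nothing. The ambiguity is real, but it does not rescue the wording, because trivial events would then be serious too (Reading B).

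A second reply is that the ethics committee's regulations may define seriousness properly. They may. As the sentence is built, however, they govern how events are reported, while the protocol's own words decide which events count as serious.

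Three stronger conclusions that a reader might draw are not supported:

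- *The committee will miss these events.* Not shown. Adverse events in general are to be recorded, and quarterly reports are not limited to serious ones.
- *No participant meets the adverse event definition.* That requires reading the definition as a trial pharmaceutical, a word that it does not contain. Participants in routine care may take medication, and the recording section plainly means to cover trial participants.
- *A between-arm comparison of harms will be wrong.* Results promises to report adverse events and does not promise to compare the arms.

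It is also fair to say that planning for suicide risk is not the same as predicting an adverse event. The statement that none is anticipated is therefore in tension with the suicide-risk section, not in strict contradiction to it.

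**Conclusion.** The point holds as a definition stated wrongly. The room that a condensed article has to leave detail to a fuller document does not cover it, because the article does state the rule. Seriousness is confused with expectedness, the adverse event definition does not fit a trial without a study drug, and on neither reading of *unexpected* can the wording separate serious events from others.

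The size cannot be stated. The article gives no event rate, and other recording and reporting routes may capture the events. What is established is that a grave, foreseeable event *can* be left out of the serious category, not that any has been. The efficacy analysis is not affected.

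The conclusion assumes that no unseen ethics committee rule overrides the protocol's definition. If one does, the protocol should cite it and drop its own wording. The correction is still warranted, because the matter is the safety of minors and the remedy is cheap.

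**What to change.** Amend the safety sections as follows:

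1. Define an adverse event as any untoward occurrence in a participant in either arm, regardless of drug exposure.
2. Define seriousness by outcome: death, threat to life, hospitalisation, persistent disability, or another medically important event, with self-harm and suicide attempt named.
3. Record expectedness and relatedness as two separate fields on the existing REDCap adverse event form.
4. Reconcile the statement that adverse events are not anticipated with Safety and Suicide Risk Reduction.
5. Check the coding of any events already logged against the new definitions.

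The cost is a short amendment, two form fields and a review of existing entries. Neither treatment nor clinical management changes. The article gives follow-up as running through October 2023, so at publication in February 2023 the new definitions could still be applied prospectively. Events recorded before the change can be re-coded where the check shows a need.
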